# Effectiveness of a Nursing Educational Intervention in Adults to Promote Control Behaviors Against Dengue: Protocol for a Randomized Controlled Trial

**DOI:** 10.2196/54286

**Published:** 2024-02-23

**Keywords:** dengue, health education, health promotion, nursing care, prevention & control

## Abstract

**Background:**

The increase in dengue cases can be attributed to social, demographic, environmental changes, or community-driven factors. In this regard, different strategies have been established in health education, using educational interventions as necessary tools for the reduction of the disease with the aim of reinforcing and stimulating the prevention and control of dengue.

**Objective:**

This study aims to evaluate the effectiveness of a nursing educational intervention for dengue control.

**Methods:**

A randomized controlled trial will be conducted with adults living in rural areas and participating in health promotion and disease prevention programs. We will enroll 116 adults. Adults will be randomized 1:1, with 58 adults assigned to the educational intervention group and 58 to the usual care group. Participants will receive 4 sessions over the course of a month, 1 week apart, and will be followed up for 1 month after the end of the educational intervention. Nursing Outcome Classification labels will be used to measure the outcomes: risk control (1902) and participation in health care decisions (1606).

**Results:**

The participants in the intervention group are expected to achieve better dengue control behaviors than those in the usual care group.

**Conclusions:**

Risk factors are fostered by the community, largely caused by artificial reservoirs or unprotected tanks in homes; also, the lack of information hinders the identification of symptomatology and the poor implementation of effective measures, and the development of standardized educational strategies can contribute to efficient and cost-effective control of the disease.

**Trial Registration:**

ClinicalTrials.gov NCT05321264; https://clinicaltrials.gov/study/NCT05321264

**International Registered Report Identifier (IRRID):**

PRR1-10.2196/54286

## Introduction

The World Health Organization, in a report for 2023, reported that between 100 and 400 million cases of dengue occur annually [1]. It also indicates that in the Americas for the year 2021, there was an incidence of 123 cases per 100,000 inhabitants, with a case fatality rate of 0.034% [2].

Dengue in general has a global annual cost of US $8.9 billion, with an average annual cost per case of US $151 in 2013 [3] and a global burden of 1.14 million disability-adjusted life years [4]. The main burden on affected countries is the enormous number of hospitalizations and sick days, with older people being the most affected population [3,5]. For the economy, the negative effects are due to the high costs of controlling epidemics and absenteeism from work and school [6,7].

In addition, dengue generates indirect costs that are usually enormous. These costs are given by the consultations or medicines taken by the members of the family nucleus [8], or by the loss of income of the patients and their families due to hospitalizations and disabilities, which at the same time reflect a reduction in the supply of work from home [9,10], not to mention the distress that the patient and his family are exposed to, generated by the doubt, uncertainty, or disability that the disease can bring. Living in low socioeconomic strata in rural areas, urbanization, global warming, and increased human mobility may be factors contributing to the increased burden of the disease [11,12].

Studies in endemic countries, specifically in Latin America, reveal a low level of knowledge about dengue among the population [13]. In Peru, Gutiérrez and Montenegro-Idrogo [14] indicated that the population has a poor level of knowledge about dengue control and prevention. In Colombia, de Maria Cáceres-Manrique et al [15] reported that the knowledge of the participants about dengue is scarce, with favorable attitudes toward control but insufficient practices, and they also consider the disease to be something normal. Likewise, other studies reflect scarce knowledge about dengue, the adoption of risky practices that favor the development of the disease, and a lack of knowledge about ways to prevent dengue [16,17].

The increase of cases in these regions, apart from having behavioral and cognitive root components, such as the behavior and cultural patterns manifested by the population, essentially related to beliefs, customs, and traditions, which sometimes determine the circumstances in which the dengue virus vector lives, also presents factors that may favor the dynamics of the disease, such as socioeconomic (level of schooling, strata, overcrowding, and lack of public services), climatic, and political factors, where there is little participation of health institutions [18,19].

Research conducted in the study setting (Montería, Colombia) has related a lack of knowledge or inadequate knowledge, unfavorable attitudes, and inadequate behaviors in relation to dengue; in addition to this, people live in homes with characteristics that favor the development and multiplication of the vector, leading to recommendations for other interventions aimed at reducing contact with the vector, taking into account the conditions in which families live [20].

The presence or multiplication of dengue cases may be mostly preceded by the inadequate application of health behaviors in the management and control of the vector, having as a background the scarcity of knowledge for the appropriation and incorporation of sanitary measures in the different environments.

In view of the lack of knowledge and control measures for dengue, the literature points to several determining factors, such as sex [13], level of schooling, and socioeconomic level, since diseases such as dengue have a greater impact on low-income populations, where the conditions for the presence of vector breeding sites are more likely to occur. A low level of education generally coincides with a lack of knowledge of the disease. Other factors include residence in rural areas, occupation, overcrowding, and a lack of public services [19].

Other factors are lack of motivation and willingness, negative attitudes (low sense of belonging), inadequate habits or inappropriate cultural practices, lack of knowledge, difficult access to health services, lack of time, perception of risk, low involvement of health institutions, and limited economic and human resources allocated to public health infrastructures [21].

Thus, the evidence points to the increase in cases of dengue fever and cognitive and behavioral factors, which will be addressed in light of Nola Pender’s Health Promotion Model (HPM). This model proposes that people interact with the environment, trying to achieve an adequate state of health, schematizing the nexus between personal characteristics and experiences, knowledge, beliefs, and situational aspects linked to the health behaviors or behaviors that are intended to be achieved [22], it raises dimensions and relationships that participate to generate or modify the health-promoting behavior [22], being the positive response that is expected to the actions carried out.

From the HPM perspective, the core concepts and subconcepts are used to achieve health-promoting behavior. Once the individual characteristics and experiences, cognitions, and affects related to the specific behavior are identified, the commitment to an action plan is expected, mediated in the research through the development of the nursing intervention that will generate a behavioral outcome, which is considered the expansion of skills in control behaviors in the prevention and management of dengue (Figure 1).

The objective of this study is to evaluate the effect of a nursing educational intervention to promote dengue control behaviors. We hypothesize that the participants in the intervention group will achieve better dengue control behaviors than participants in the usual care group.

**Figure 1 figure1:**
[figure not shown]
Description of the conceptual elements for the study of health promoting behavior.

## Methods

### Study Design

A randomized controlled trial that follows the guidelines of SPIRIT (Standard Protocol Items: Recommendations for Interventional Trials) is used [23]. The study protocol was registered in ClinicalTrials.gov (NCT05321264).

### Randomization and Blinding

Simple randomization into groups of equal size will be performed using the EPIDAT 4.2 program (Department of Health, Council of Galicia, Spain). Study participants will be randomized 1:1 to receive either the educational intervention or usual care. The randomization and allocation concealment will be carried out by the principal investigator. A centralized telephone randomization system will be used for masking [24]. With respect to blinding, the nurse who will perform the intervention will be blinded and will not know the outcome indicators of the study; the outcome assessors will be blinded and will not know to which group (intervention or control) the participants belong.

### Participants, Setting, and Sample

The study participants are rural residents attending health promotion and disease prevention programs in a health care institution located in the municipality of Montería. It is a city in Colombia and capital of the department of Córdoba. It has 490,935 inhabitants and is considered a cattle-raising town.

Participants will be recruited during the opening hours established by the health institution. A sample size of 116 (58 participants for each group) was calculated according to the following parameters: effect size: an expected difference of 0.5 in the score of the nursing outcome labels between both groups [24], a statistical power of 90%, an α type error of 5%, a SD of the outcome scores of 1.0, an average correlation between the first and second evaluations of 0.3, an intervention/control ratio of 1:1, and a loss adjustment of 20%. Stata (version 16.0; StataCorp) software was used for this purpose.

### Procedures

#### Eligibility Criteria

Persons older than 18 years of age, residing in a rural area of the municipality of Monteria in an endemic area with dengue or with exposure to dengue, attending health promotion and disease prevention programs of a health institution with an initial score ≤a 3.5 in the Nursing Outcome Labels (NOC) risk control (1902) and participation in health care decisions (1606), will be included in the study [25].

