### Data Analysis

The information will be tabulated using the EpiData program, and the Stata software will be used for statistical analysis, following the principle of intention-to-treat analysis, which allows the patients to be analyzed as they were originally assigned or randomized [37]. Statistical hypothesis tests will be performed with an α level of 5%. A descriptive analysis of the baseline variables will be made to observe the behavior in each of the groups, using the student 2-tailed *t* test and the Fisher exact test. Categorical variables will be presented with absolute and relative frequencies. Quantitative variables with normal distribution will be presented with mean and SD, and for variables that do not comply with the principle of normal distribution, they will be presented with median and IQR (IQR=Q3–Q1). Normality will be assessed using the Kolmogorov-Smirnov test.

Baseline variables will be compared between the control group and the intervention group. The chi-square test will be used for categorical variables. The student *t* test will be used to compare the means in the 2 groups when the normality assumption is met, and otherwise, the nonparametric Mann-Whitney *U* test will be used.

To control for possible confounding variables, a statistical adjustment will be made through an analysis of covariance with their respective 95% CIs.

The effect of the intervention will be measured through analysis of covariance by means of the delta value or difference of the NOC label score between the 2 comparison groups.

Paired *t* tests will be performed to observe separately how each group fared before and after the intervention and at follow-up.

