### Limitations

Length of follow-up, cointerventions, and attrition during the study are anticipated limitations. To reduce these limitations, the selection of participants will be controlled by random assignment to the intervention, specific eligibility criteria for entry into the study, and intention-to-treat analysis. Both the intervention and outcome assessors will receive appropriate training. Masking and adjustments to the statistical analysis will be performed as needed. Health care professionals will be sensitized to avoid cointervention in the study. The principal investigator will be the study supervisor and will not be involved in intervention delivery or outcome assessment.

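### Adults are randomised individually with no stated limit per household, although the intervention targets the shared home; housemates split across arms would dilute the effect (minor)

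*Protocol article*

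**What the plan says.** **Unit of allocation.** Under Randomization and Blinding, the unit is the person: "Study participants will be randomized 1:1 to receive either the educational intervention or usual care". Randomisation is simple, into groups of equal size.

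**Who may enter.** Under Participants, Setting, and Sample, recruitment takes place at one health institution in Montería. Eligibility Criteria admits "Persons older than 18 years of age, residing in a rural area of the municipality of Monteria" who attend its prevention programmes and score 3.5 or less on the two nursing outcome labels. All of these conditions apply to the person; none refers to the household.

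**What is taught.** Under The Study Intervention, session 1 covers breeding sites found around a house, such as tanks, vases, pet bowls and plastic containers. Session 3 seeks commitment to preventive care of the person, the home and the surroundings. Session 4 reviews support networks, family among them. Delivery is individual and face to face, with a standard booklet. The Discussion (Principal Result) itself ties dengue to sanitation in the household.

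**Analysis and limitations.** Data Analysis describes analysis of covariance and t tests on individuals. On limitations the article says: "Length of follow-up, cointerventions, and attrition during the study are anticipated limitations". Passage of the intervention between arms is not mentioned.

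**The concern.** Nothing in the stated rules stops two adults from one home from enrolling and being allocated separately. If one is assigned to the intervention and the other to usual care, they share the same tanks and containers and may share the booklet and what was learned. The control's risk control score may then rise for reasons that belong to the other arm.

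This pulls the estimated difference towards zero, so a real benefit could be understated or missed. Intention-to-treat analysis does not help, because the control is analysed correctly as a control but has been partly exposed. The safeguard under Limitations, sensitising health professionals against cointervention, does not reach what passes between people who live together.

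**Working it through.** **Inputs from the article (Participants, Setting, and Sample):** "an expected difference of 0.5 in the score of the nursing outcome labels between both groups"; "a SD of the outcome scores of 1.0"; 90% power; 5% alpha (taken as two-sided, since the sample-size text does not say); correlation 0.3 between evaluations; 1:1 allocation; 20% allowance for loss. Data Collection and Measures gives one baseline and two later measurements.

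**Step 1: reproduce N = 116.** The article does not state its formula. With one baseline, two follow-ups and baseline adjustment, the variance factor is (1 + 0.3)/2 − 0.3² = 0.65 − 0.09 = 0.56.

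n per arm = 2 × 0.56 × ((1.960 + 1.282) × 1.0/0.5)² = 47.07, rounded up to 48. Then 48 × 1.2 = 57.6, rounded up to 58 per arm, or 116 in total. No design effect or household term is needed to reach the figure, so it is a sample size for independent individuals.

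**Step 2: power without dilution.** With 48 analysed per arm, SE = √(2 × 0.56/48) = 0.1528. Power = Φ(0.5/0.1528 − 1.96) = 90.5%.

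**Step 3: dilution.** Two assumptions are not in the documents:
- q, the share of participants who live with another participant, all in pairs: 5% to 40%.
- c, the share of the effect that a control housemate picks up: 0.5 as the central value, 1.0 as the extreme.

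With 48 + 48 people, a given pair is split with probability 48/95 = 0.505. The expected difference is therefore 0.5 × (1 − q × 0.505 × c), and power = Φ(difference/0.1528 − 1.96).

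| q | c | Expected difference | Power, 48 per arm | N restoring 90% (same × 1.2) |
|---|---|---|---|---|
| 0 | – | 0.500 | 90.5% | 116 |
| 5% | 0.5 | 0.494 | 89.8% | 118 |
| 10% | 0.5 | 0.487 | 89.1% | 120 |
| 20% | 0.5 | 0.475 | 87.4% | 128 |
| 40% | 0.5 | 0.449 | 83.7% | 142 |
| 40% | 1.0 | 0.399 | 74.3% | 178 |

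**Step 4: does ignoring the household distort the standard error?** Same-arm pairs make an independence analysis too optimistic, and split pairs make it too cautious. With individual allocation the expected design effect is 1 + q × ICC × (2 × 47/95 − 1) = 1 − 0.0105 × q × ICC. At the extreme of q = 40% and an assumed ICC of 0.5, this is 0.998. The two kinds of pair nearly cancel. A design effect of up to 1 + 0.4 × 0.5 = 1.20 would need every pair to fall in the same arm, which this randomisation does not do.

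**The case against.** **The risk is conditional and may be small.** No passage gives a co-enrolment rate. A q of 40% means about 23 pairs among 116 people, which is a lot for one recruiting site. With up to 20% co-resident and half transfer, the loss is at most about three points of power. If nobody were lost to follow-up, 58 per arm would start from 94.9%, which leaves room for some dilution. All of this stands, and it is why the point is minor.

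**Transfer is unlikely to be complete.** Sessions are delivered to one person, and both outcomes describe personal behaviour. A housemate who covers a tank does not obviously raise a control's score for participation in health care decisions. The article also does not say that the booklet is taken home. This stands too: half transfer is a reasonable central case, and full transfer is an outer bound.

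**A household rule may exist in the full protocol.** That is possible, since the eligibility text is short. But the article does state its criteria and its unit of randomisation, and as written they permit split households. An analysis plan could not undo the exposure afterwards.

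**Readings that go too far.** A reader might infer three further things:
- *That the standard errors will be too small.* Step 4 shows that they are not, in expectation.
- *That the problem is beyond repair because household is not recorded.* The baseline form is described only by examples, so the article does not show that address or household is left out.
- *That session 4 brings relatives into the intervention.* The text has the participant review available support; no relative is said to attend.

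**Conclusion.** The point holds as a minor design weakness. The stated rules allow housemates to be enrolled and split between arms in a trial whose content is largely about the home. About half of any such pairs would be split, and the resulting bias runs towards no effect.

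Its size rests wholly on assumed co-residence and transfer. With half transfer, power falls from 90.5% to between 89.8% (5% co-resident) and 83.7% (40%); about 74% is the extreme of the range examined.

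A reader might instead quote a fall from 81% to 72% or 62%. Those figures (80.6%, 71.9% and 61.7%) come from 58 per arm, a single-follow-up variance factor of 1 − 0.3² = 0.91, and 10% or 20% of controls gaining the whole effect. The documents do not support leading with them. The starting value belongs to a separate question about the sample-size model, complete transfer is a worst case, and 20% of controls exposed implies about 40% of participants co-resident.

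**What to change.** Add one sentence to Eligibility Criteria: only one adult per household may take part, namely the first eligible person who consents. Check this with a question on address at screening, before allocation, so that the choice of household member cannot depend on the arm.

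This removes split pairs and same-arm pairs together. Independence then holds, the planned analysis is unchanged, and N stays at 116. The cost is one line of text, one screening question and slightly slower recruitment.

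The alternative is to keep relatives and randomise whole households, with household-robust or mixed-model standard errors. With the same × 1.2 allowance and a design effect of 1 + q × ICC, that needs between 116 (q = 5%, ICC = 0.1) and 138 (q = 40%, ICC = 0.5) participants. It is more work for no clear gain here.

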#### The Study Intervention

The educational nursing intervention in adults to promote dengue control behaviors, in terms of its structure, will follow the guidelines established by Sidani and Braden [26]. In addition, it will have as a theoretical reference Nola Pender’s HPM, which is articulated for the phenomenon under study, to allow reaching a health-promoting behavior, which lies specifically in the expansion of skills in control behaviors in the face of dengue. The intervention contemplates 3 active ingredients that influence dengue control behavior: an educational component, behavioral support, and attitudinal support (Textbox 1).

Content of the intervention.
**Active ingredients and components**
Session 1: educational componentGeneral information on dengue: definition of the disease, etiological agent, mosquito life cycle, modes of transmission, period of transmissibility, and personal and environmental risk factors (tanks, flower vases, pet drinkers, and plastic containers).Session 2: educational componentDengue overview: health threats, clinical manifestations, diagnostic aids, treatment, prevention and control strategies, and barriers that may prevent the implementation of effective measures.Session 3: behavioral supportCommitment to the implementation of preventive strategies (personal, home, and environmental care), achievements obtained with the implementation of dengue strategies, self-control in dengue decision-making, and lifestyle changes.Session 4: attitudinal supportMain support networks that people can find in their environment: family, friends, health, and community resources. How to take advantage of available resources?

The intervention will consist of 4 face-to-face meetings with an interval of 1 week for 1 month, each lasting 45 minutes (Textbox 2). The first session will include an educational component and address issues related to dengue, etiological agents, transmission mechanisms, and personal and environmental risk factors. The second session will cover topics such as health threats, clinical manifestations, diagnostic aids, treatment, prevention and control strategies, and barriers that may prevent the application of effective measures against dengue, also belonging to the educational component. The third session will cover personal care practices, home and environment care, and lifestyle modification, which correspond to behavioral support. Final, the fourth session covers attitudinal support, which will review support networks and the use of resources.

General characteristics of the intervention.Objective: increase knowledge and application of dengue control behaviors.Duration of the intervention: 1 monthNumber of sessions: 4 sessionsFrequency: once a week for a period of 1 month.Environment: institution providing health services in rural areas (promotion and prevention program).Delivery strategies: individual, face-to-face, standardized educational material, and use of digital tools.Receiver: adult who meets inclusion criteria.Provider: qualified and trained nurse, with previous performance verification (does not work in health institution).Outcome measures: risk control and participation in health care decisions.

The intervention will be delivered in a personalized, face-to-face manner [27], and standardized educational material (booklet) will be used [28-30]. It also indicates that feedback, reviews of key points, and commitments will be made in each session that is held.

